**Fig. 3 Fig3:**
[figure not shown]
Data collection scheme. Each intervention will be performed for 8 min prior to starting the cannulation procedure to just after starting haemodialysis. *Will be measured only on HD4, HD7, HD10 and HD13

### Data collection and follow-up

#### HD1

##### Baseline information

Baseline information—including age, gender, height, weight, duration of haemodialysis, history of smoking, medication, type and location of blood access, cause of kidney dysfunction, history of diseases (including skin disease, chronic heart failure, collagen disease, diabetic complications, liver disease, cancer, and AIDS, which are used to calculate Charlson Comorbidity Index [53]) and music preferences—will be collected.

##### State-Trait Anxiety Inventory (STAI) -Y-2

The STAI is a commonly used measure to assess trait and state anxiety [54–56]. The State-Trait Anxiety Inventory-JYZ (Jitsumukyoiku-Shuppan Co., Ltd., Tokyo, Japan) will be used. Each patient will complete this measure on a tablet PC. The STAI comprises 40 questions. The first 20 measure state anxiety, and the latter 20 measure trait anxiety. This measure has been previously validated for assessing anxiety during music therapy [57]. Whereas state anxiety can be considered more situational in nature and often is associated with the arousal of the autonomic nervous system, trait anxiety can be thought of as a worldview that an individual uses when coping with situations in his or her environment [58]. The first 20 items will be administered during each session, whereas the latter 20 will be administered only at HD1.

#### HD2–13

##### Conditional information regarding the cannulation

Conditional information regarding the cannulation will also be collected. This includes planned removal of water volume, weather (reported to have a relationship with the status of anxiety [59, 60]), use of topical analgesics, use of oral analgesics within 6 hours prior to the cannulation, the number of years that the operator has conducted dialysis, operator’s occupation (doctor, medical engineer, or nurse), gauges of the needle used for cannulation (on both the removing side and returning side), cannulation needle shape, number of cannulations (occurrence of cannulation failure), single needle used, change of operator, and posture when the patient was punctured.

##### Primary outcomes

The primary outcome is the VAS pain score during the cannulation. The VAS comprises a 100-mm line. The leftmost value is 0, which indicates no pain. The rightmost value is 100, which indicates maximum pain. Patients mark a point with their finger on the screen [61]. Although patients receive at least two cannulations during each dialysis session, pain will be evaluated only once per session. The maximum pain of the cannulations will be scored.

##### Secondary outcomes

The secondary outcomes include BP, HR, VAS anxiety score (evaluated on HD2–HD13), STAI (state scale: Y-1) and S-AMY (evaluated on HD4, HD7, HD10 and HD13).

BP and HR will be measured immediately after putting on the headphones and after the puncture procedure (once each time) via an electronic sphygmomanometer attached to the dialysis console. Each patient will be measured in the same posture (sitting up or supine) throughout the procedure.

Anxiety will be assessed via VAS on a tablet PC just after starting haemodialysis. The anxiety scale is in the same format as the pain scale and will be completed in the same manner [61].

Patients’ state anxiety via the STAI (Y-1) will be assessed immediately after the puncture during the No-sound period, Music period, and White noise period, respectively.

S-AMY fluctuates on the basis of autonomic nervous system activity, thus making it a reliable and objective marker of mental and physical stress [62–64]. With S-AMY, anxiety can be evaluated not only subjectively by VAS and STAI but also objectively. A salivary amylase monitor (Nipro, Co., Osaka, Japan) and a corresponding test strip (Nipro, Co.) will be used. Saliva is collected by a test strip placed under the tongue for about 30 s, and amylase concentration in the saliva is immediately measured.

S-AMY levels will be evaluated prior to and after the cannulation at the end of the No-sound period, Music period, and White noise period, respectively. After each intervention period, adverse events will be assessed.

### Safety assessments

As cannulations are a regular procedure in a haemodialysis session and listening to sounds is not a major invasive procedure, there is no expected harm for patients to participate in this intervention, as no negative effects of music therapy have been reported in prior studies. The saliva collection method is also harmless. Nevertheless, participant safety will be ensured during the protocol.

### Sample size

We conducted a pilot two-arm randomised controlled trial at four facilities, whereby eight haemodialysis patients were assigned randomly into either of the two groups: Group 1 listened to Mozart, and Group 2 listened to the news on the radio. The primary outcome was cannulation pain evaluated via a VAS. A previous review suggested that patients who record a baseline VAS score of more than 30 mm might indicate at least moderate pain [65]. Moura and colleagues reported that 20% of the haemodialysis patients suffer from pain, indicated by a VAS pain score of more than 30 mm [4]. In our pilot study, the mean VAS results were 20.5 mm in Group 1 and 25.4 mm in Group 2. All VAS scores were normally distributed, and the standard deviation was 12.0 mm. Based on results of clinical trials of analgesic agents [66, 67] and a cost-benefit performance of music therapy, a difference of 4.9 mm was considered to be clinically significant and was used for the sample size design. From these results, we computed that 95 patients are needed to observe a treatment effect based on this effect size at a power of 80% with a two-sided significance level of 5%. Assuming participant attrition, we will recruit a total of 120 participants. As the proposed study is a crossover trial wherein the statistical power is assumed to be greater than that of a two-arm design, we believe that our study is adequately powered.

### Randomisation

Haemodialysis patients who meet all inclusion criteria and do not meet any of the exclusion criteria will be randomly assigned to the Early-sequence group or the Later-sequence group during the enrolment period (HD1). The permuted block randomisation will be performed by using REDCap [53, 54]. Only selected staff at each facility will be authorised to access REDCap for patient randomisation.

### Blinding procedure

We will explain to the patients that the first period and third period are no-sound periods and that the second period and the fourth period are sound-listening periods (music or white noise) when we are obtaining informed consent. Operators will also receive these explanations in advance; moreover, during the no-sound period, they will be informed that it is a no-sound period on the tablet’s screen. The reason for such an explanation is to prevent patients from mistakenly believing it is a no-sound period if equipment malfunctions or if the volume of the sound is too low in the initial setting. Of course, patients and operators will not know in advance the results of allocation (i.e., arrangement of music period and white noise period in the second and the fourth week) to maintain study blindness.

Blinding participants to the allocation and evaluation of the VAS and STAI scores is not possible, as patients will be aware of what they will be hearing and the specific evaluations conducted. However, if participants are told that the purpose of this study is to assess the effectiveness of the music therapy, a demand characteristic, which refers to participants playing the role of a ‘good participant’ by altering their behaviour in order to obtain the researchers’ expected outcome, could emerge, resulting in information bias [68, 69]. Thus, we will not tell participants that we are assessing the effectiveness of a music intervention per se. In essence, participants will not be aware of whether music or white noise will be more soothing. Specifically, we will state, ‘Both sounds are considered effective, and we will examine which one is more effective’, in order to alleviate any potential demand characteristics.

As the patients will not be blinded to the treatment allocation, it is important that the person evaluating the outcome measure of VAS be blinded to the study. Although the outcome evaluator needs to also perform the randomisation, we created an automated process in REDCap to randomly choose and play either the music or the white noise without letting the study personnel know which sound is being played. Along with randomisation, they will be blinded to the music operation and evaluation procedures to measure the VAS as follows. The operator will dispense the sounds from REDCap; however, the REDCap screen will not indicate whether music or white noise is being played. Participants will wear a headset while the music or white noise is being played, and they will be instructed not to tell the study personnel what sound is being played. The patients will provide VAS and STAI scores via an online questionnaire via REDCap. Therefore, the operator will not see these results. Each haemodialysis facility will have designated staff with access to the REDCap and enter the data.

### Data management

A software toolset and workflow methodology for electronic data collection and management (REDCap) will be used. REDCap servers are managed by Osaka City University using cloud servers. All web-based information transmission will be encrypted. All protocols, consent forms, and data will be stored in the REDCap system. Data monitoring will be performed by an independent data coordinating centre. Two independent statisticians will be able to access the trial dataset.

### Analyses

#### Analysis of VAS pain scores during the cannulation

A set of outcome variables, which includes the VAS pain score as the primary outcome and the VAS anxiety score, STAI score, and S-AMY as the secondary outcomes, will be assessed during a single dialysis session. Each study period will last for a week including three dialyses. Patients will undergo two study periods; thus, each patient will be assessed for six sets of the outcome variables (three in the music period and other three in the white noise period).

A linear mixed model will be applied to compare the means of the three repeated outcome measures between the music and the white noise periods. For the outcome that accompanies the baseline measures, the mixed model will compare the mean of three repeated change scores between the two periods. Compound symmetry was used for variance-covariance to estimate dependency among the repeated measures. Two-sided significance level will be set at 0.05. The normality of the residuals will be confirmed via Q-Q plots, and the mathematical transformation of the outcome variable will be performed if necessary. The mixed-model approach was chosen on the basis of a Monte Carlo simulation study in order to compare the statistical power of three different analytical strategies, which include the following (see Additional file 2).
Paired *t* test to compare the two means of three pain scores between the two periods. (The unit of observation in the analysis is the within-patient mean score of the three scores; the analysis includes two mean scores per patient.)Linear mixed model to compare the two means of the three pain scores between the groups. (The unit of observation is the same as 1.)Linear mixed model to compare the six pain scores between the two periods. (The unit of observation is the pain scores; the analysis includes six observations per patient.)

The third approach was chosen because it appeared to be superior to other approaches, as it provides the largest statistical power to detect statistical significance while controlling for type I error. In addition, the direct inclusion of all six observations will allow us to control for time-dependent confounders, such as personnel effect from the operator who performs the cannulation.

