#### Missing data

Data collection will be interrupted. When the study resumption becomes possible, data collection will be resumed.

* When a participant is hospitalised.

* When the haemodialysis access is narrowed and a percutaneous transluminal angioplasty (PTA) is performed.

* When the haemodialysis access is occluded and blood flow restarts via non-surgical treatment such as massage or PTA.

* When study continuation is difficult because of unavoidable circumstances to participants.

* When study continuation is difficult because of unavoidable circumstances to medical staff.

As a mixed effect model allows for a robust analysis of missing data [70], we will use all available data for the analysis. In the event of any other situations, researchers will decide on a response after consultation.

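### The primary crossover model, as described, names no fixed effect for week 2 versus week 4, so a time shift can bias the music effect if the two sequences lose unequal numbers

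*Protocol article*

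**What the plan says.** The Design section of the protocol article allocates patients equally to an Early sequence (music in week 2, white noise in week 4) or a Later sequence (the reverse), with no-sound weeks before each.

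The Analyses section, under VAS pain scores, describes the primary model: "A linear mixed model will be applied to compare the means of the three repeated outcome measures between the music and the white noise periods". Three strategies were compared by simulation, and the one chosen is "Linear mixed model to compare the six pain scores between the two periods", with six scores per patient and compound symmetry. In that section the word period means the listening condition, not the calendar week. The benchmark paired t test has no week effect by construction. The section adds that six observations make it possible to control time-dependent confounders, and the only example given is the operator.

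On incomplete data, the Missing data section says "we will use all available data for the analysis". The Dropout section rules out replacement of dropouts. The Analysis set section keeps any patient with at least one score under either condition. The limitations in the Discussion deal with carry-over but not with a period effect.

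**The concern.** Which condition falls in week 2 and which in week 4 is the factor that is randomised, so calendar period belongs to the design and is not an optional covariate. A model with treatment alone handles a general shift between those weeks in two ways.

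- **Variance.** Within each patient the shift adds to the treatment difference in one sequence and subtracts from it in the other. Without a period term, that spread is counted as residual error.
- **Bias.** The additions and subtractions cancel only if the sequences contribute equally. If they do not, part of the shift is read as a treatment effect.

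The plan leaves room for a shift. Patients are enrolled because they report pain, which allows regression to the mean, and interrupted patients may resume later. It also leaves room for unequal loss: "Assuming participant attrition, we will recruit a total of 120 participants" against 95 needed implies an allowance of 1 − 95/120 = 20.8%, without replacement. At stake is the type I error of the primary test, which the article says was controlled when the model was chosen.

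**Working it through.** **Inputs from the protocol article.** Effect: "a difference of 4.9 mm was considered to be clinically significant and was used for the sample size design". Spread: "All VAS scores were normally distributed, and the standard deviation was 12.0 mm". Error rates: "at a power of 80% with a two-sided significance level of 5" percent. Result: "we computed that 95 patients are needed to observe a treatment effect".

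**Assumptions, because the article gives neither.** Within-patient correlation ρ (0 to 0.7 for power, 0.5 elsewhere) and a week 4 minus week 2 shift π (2, 5 or 10 mm). The calculations use complete six-score data and no patient-by-period variance, unless stated.

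**1. The plan's own figure.** 2 × (12 × (1.960 + 0.842)/4.9)² = 94.1, so 95. The figure is reproduced. It is the size per arm of a parallel comparison. It is also the total for a paired comparison of one score per condition with ρ = 0, where the SD of the difference is 12√2. A period term does not change it.

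**2. Standard error.** The within-patient variance is 144 × (1 − ρ) = 72 at ρ = 0.5. With 95 patients and three scores per condition, SE = √(2 × 72/(3 × 95)) = 0.711 mm. Without a period term the residual variance rises by about (π²/4) × 6/5:
- π = 5: 72 + 7.5 = 79.5, reported SE 0.747
- π = 10: 72 + 30 = 102, reported SE 0.846

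**3. Power for the six-observation model, 95 patients.**

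| True effect | ρ | Shift | Without term | With term |
|---|---|---|---|---|
| 4.9 mm | 0 | 10 mm | 99.7% | 99.8% |
| 4.9 mm | 0.3 or more | up to 10 mm | about 100% | about 100% |
| 2 mm (simulated) | 0.5 | 5 mm | 78.3% | 79.2% |
| 2 mm (simulated) | 0.5 | 10 mm | 74.4% | 81.2% |

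**4. Bias among completers.** Music minus white noise has expectation τ − π in the Early sequence and τ + π in the Later sequence, where τ is the true effect. The pooled estimate is therefore off by π × (nE − nL)/(nE + nL) in size.

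| Completers Early/Later | π = 2 | π = 5 | π = 10 |
|---|---|---|---|
| 60/60 | 0 | 0 | 0 |
| 50/45 | 0.11 mm | 0.26 mm | 0.53 mm |
| 55/40 | 0.32 mm | 0.79 mm | 1.58 mm |

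If scores rise from week 2 to week 4 and more Early patients remain, the bias favours music. It reverses if either sign reverses.

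**5. Type I error (4,000 simulated trials, ρ = 0.5).**

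| Completers | Shift | Without term | With term |
|---|---|---|---|
| 48/47 | 5 mm | 4.2% | 5.1% |
| 48/47 | 10 mm | 2.3% | 5.8% |
| 55/40 | 5 mm | 16.8% | 5.5% |
| 55/40 | 10 mm | 44.7% | 5.0% |

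A normal approximation, Φ((b − 1.96·SE reported)/0.711) + Φ((−b − 1.96·SE reported)/0.711) with b the bias, agrees. At 55/40 and 5 mm it gives Φ((0.789 − 1.462)/0.711) + Φ((−0.789 − 1.462)/0.711) = 17.3%. At 50/45 and 5 mm it gives Φ((0.263 − 1.464)/0.711) + Φ((−0.263 − 1.464)/0.711) = 5.3%. The inflation therefore needs a clear imbalance.

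**6. Keeping early leavers in the analysis.** With 60/60 randomised, leavers kept with their week-2 scores, ρ = 0.5 and a 5 mm shift, losses of 12 and 13 give a bias below 0.05 mm. Losses of 8 and 17 give 0.41 mm, and losses of 5 and 20 give 0.69 mm. The retained week-2 data reduce the completer bias slightly but do not remove it.

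**The case against.** The strongest objection is that the omission is read from silence. The article gives the contrast, the unit and the covariance, not a full list of fixed effects. Additional file 2 and any analysis plan are not shown, and the remark on time-dependent confounders leaves room for further covariates. This stands in part: a reader might infer that a period term has been ruled out, and the article does not say so. It does support a narrower statement. The primary method is set out in some detail, and the randomised week factor is not in it.

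A reader might also infer that any time trend seriously wastes power. A patient-level paired analysis of a 2.5 mm effect under a 5 mm shift can show power falling from 84% to 73%. That calculation uses an analysis the plan rejected and about half the design effect. For the chosen model at 4.9 mm almost nothing is lost.

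A third tempting reading is that attrition will unbalance the sequences. Allocation is equal and in permuted blocks, no attrition rate is stated, and nothing suggests that loss depends on sequence. Imbalance is possible, not certain.

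Finally, a 5 mm shift exceeds the whole design effect, in patients with more than six months of dialysis and a no-sound run-in week. This is fair. The shift is an assumption, and at 2 mm the bias is only 0.11 mm (50/45) or 0.32 mm (55/40).

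**Conclusion.** The point holds in a limited form. As described, the primary model contrasts music with white noise and names no effect for week 2 versus week 4, although order is what is randomised.

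The cost in power is negligible at 4.9 mm and modest for smaller effects. The bias matters more, but it needs both a period shift and unequal sequences. Under an assumed 5 mm shift it is small at 50/45. At 55/40 the 0.79 mm bias is about one standard error, and it is enough to raise the type I error to about 17%. With near-equal sequences the test errs slightly on the conservative side.

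These sizes rest on ρ = 0.5, the assumed shift, complete six-score data among completers and no patient-by-period variance. The direction of both effects does not depend on those values. The change is worth making because it removes the dependence on equal loss at almost no cost.

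**What to change.** State in the primary analysis that the six-observation mixed model contains fixed effects for treatment (music or white noise) and for calendar period (week 2 or week 4). Use a separate word for the listening condition, so that period has one meaning. If the term is already in the analysis plan or Additional file 2, a sentence confirming this is enough.

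A sequence term is optional, since it is a between-patient term and does not remove the period shift. Whether to add a patient-by-period random effect is a separate question about the covariance structure and is not needed here.

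The cost is one degree of freedom and one line of text. No new data are needed, and the stated 95 patients do not change.

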Figure 3 shows the flow of the interventions performed each day during implementation. First, blood pressure (BP), heart rate (HR) and salivary amylase activity (S-AMY) will be measured. Then, the patient wears the headphones connected to the tablet PC. Eight minutes after the initial listening period (Music, White noise periods or No-sound), the operator will prepare for the haemodialysis access cannulation and then cannulate the haemodialysis access. Immediately after the cannulation, BP and HR will be measured again. After connecting the cannula to the haemodialysis machine, the patient will stop listening and report his or her VAS pain score, VAS anxiety score, and State-Trait Anxiety Inventory (STAI). Both the time from the start of listening to the sound and the time of the end of the intervention will be recorded by REDCap. The patients enter his or her VAS pain score, VAS anxiety score, and STAI directly into the REDCap system on a tablet PC. This procedure ensures data independence, as the operator and investigator will be blinded to patients’ reports. S-AMY is also measured at this time; however, S-AMY and STAI are assessed only during haemodialysis (HD)4, HD7, HD10 and HD13.

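### BP, HR and S-AMY are planned as unadjusted change scores, where adjusting for the pre-cannulation value is at least as precise; the rule does not fit S-AMY, and the BP/HR baseline timing is contradictory

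*Protocol article*

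**What the plan says.** The section Analysis of VAS pain scores during the cannulation plans a linear mixed model comparing the music and white noise periods. For outcomes with a baseline it adds: "For the outcome that accompanies the baseline measures, the mixed model will compare the mean of three repeated change scores between the two periods". On the covariance it says: "Compound symmetry was used for variance-covariance to estimate dependency among the repeated measures". No baseline covariate is named, and a transformation is allowed if the residuals call for it. The sentence does not name the outcomes it covers. BP and HR are absent from that section's outcome list, although Secondary outcomes includes them.

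On the timing of the first BP/HR reading, Study protocol has: "First, blood pressure (BP), heart rate (HR) and salivary amylase activity (S-AMY) will be measured. Then, the patient wears the headphones". Secondary outcomes has: "BP and HR will be measured immediately after putting on the headphones and after the puncture procedure".

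For S-AMY, Secondary outcomes has: "S-AMY levels will be evaluated prior to and after the cannulation". Study protocol restricts the sessions: "S-AMY and STAI are assessed only during haemodialysis (HD)4, HD7, HD10 and HD13". Table 1 agrees with that restriction.

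**The concern.** A change score subtracts the whole pre-value whatever its relation to the post value. Unless the best-fitting within-patient slope happens to be 1, this leaves noise in the outcome that a covariate would remove. Patients cannot be blinded to the sound, and the Discussion gives the subjectivity of the VAS as the reason for adding an objective marker. It also links a BP effect to possible use in hypertension. These outcomes should therefore not lose precision needlessly.

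Two further defects affect the same sentence. It assumes three change scores per period, which S-AMY does not have. For BP and HR, the reading to be subtracted is defined in two incompatible ways.

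**Working it through.** **Which outcomes are covered.** VAS pain, VAS anxiety and the state scale of the STAI are reported only after cannulation. BP, HR and S-AMY are read before and after it in the same session. The no-sound weeks are unlikely to be the intended baseline: every repeated outcome is measured in them, so the sentence would then single out nothing. The rule therefore falls on BP, HR and S-AMY.

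**The plan's own figure.** There is none for these outcomes: no SD, correlation or precision is given. The only calculation is for VAS pain: 2 × (1.960 + 0.842)² × 12.0² / 4.9² = 94.15, rounded up to 95, which is a per-group size for a parallel comparison. It does not bear on this point and serves below only as a yardstick.

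**Precision in general.** Let b be the best within-patient slope of post on pre. Then

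Var(post − pre) = Var(post − b·pre) + (1 − b)² · Var(pre).

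The last term cannot be negative. The change score can therefore equal the adjusted analysis (at b = 1) but not beat it, apart from the one or two degrees of freedom spent on the covariate terms.

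**Equal pre and post variance s², within-patient correlation r (both assumed).**

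- Post value alone: s²
- Change score: 2s²(1 − r)
- Covariate-adjusted: s²(1 − r²)
- Adjusted relative to change: (1 − r²) / [2(1 − r)] = (1 + r)/2

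| assumed r | change / post alone | adjusted / change (variance) | SE ratio | patients the change score needs to match 95 adjusted |
|---|---|---|---|---|
| 0.3 | 1.40 | 0.65 | 0.81 | 95/0.65 → 147 |
| 0.5 | 1.00 | 0.75 | 0.87 | 95/0.75 → 127 |
| 0.7 | 0.60 | 0.85 | 0.92 | 95/0.85 → 112 |
| 0.9 | 0.20 | 0.95 | 0.97 | 95/0.95 = 100 |

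Below r = 0.5 the change score is less precise than ignoring the pre-value.

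**Simulation check.** A two-sequence crossover was simulated with 96 patients, 3000 replicates, a within-patient estimator and equal variances. At r = 0.3, 0.5, 0.7 and 0.9 the adjusted/change variance ratio was 0.63, 0.75, 0.86 and 0.96 with three sessions per period, and 0.66, 0.75, 0.86 and 0.97 with one. All estimators were unbiased.

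**Unequal variances.** Take post SD = 1.3 × pre SD (illustrative) and pre variance 1. The change-score variance is 1 + 1.69 − 2.6r and the adjusted variance is 1.69(1 − r²).

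- r = 0.5: 1.2675 / 1.39 = 0.91
- r = 0.7: 0.8619 / 0.87 = 0.99

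The best slope is 1.3r, so the gain falls to nothing as 1.3r approaches 1.

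**S-AMY.** Each sound week has three sessions, HD5–7 and HD11–13, but S-AMY is measured only at HD7 and HD13 within them. That is one pre/post pair per period, not three.

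**BP/HR timing.** Study protocol puts the first reading before the headphones go on; Secondary outcomes puts it just after. Both describe the same reading, so both cannot hold. For S-AMY, Study protocol places the first sample before the headphones, and Secondary outcomes says only that it precedes cannulation. Those two statements are compatible.

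**The case against.** The strongest case against is that this is a preference about efficiency, not an error. In a randomised crossover with a clean baseline the change score is unbiased, only secondary outcomes are touched, and the article makes no power claim for them. That stands: the issue is precision, and a reader should not infer that the change-score analysis is invalid.

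The size of the gain has no source in the article. The pre and post readings are separated by about 8 minutes of listening plus the cannulation, so a high r cannot be excluded, and equal variances are also assumed. A reader might take the loss as a known 15% to 35%; the article does not support that.

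An article may also leave its covariate list to an analysis plan, and adding the pre-value to a change-score model gives the same treatment estimate as modelling the post value with that covariate. The wording therefore does not rule the adjustment out. It does, however, state a change-score comparison and name no such covariate. The power comparison said to support the chosen model is described for pain scores only, and these have no pre-value.

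A tempting stronger reading is that the BP/HR baseline is contaminated by the music. No section says sound is playing at that reading. Headphones are worn in both compared periods, so a common headphone effect cancels in the music versus white noise contrast. Contamination arises only if sound had already started. In that case the covariate analysis would be affected too, so the timing has to be settled first. Nor does the timing conflict extend to S-AMY.

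**Conclusion.** The point holds for three secondary outcomes and leaves the primary VAS pain analysis untouched.

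- **Precision.** Adjustment is at least as precise as the planned change score, apart from one or two degrees of freedom. With equal variances it removes 35% of the variance at r = 0.3 and 5% at r = 0.9. With a post SD 1.3 times the pre SD it removes about 1% at r = 0.7. These sizes rest on assumed values of r and of the variance ratio.
- **S-AMY.** The rule cannot be applied as written. This rests on the article alone.
- **BP/HR baseline.** The two sections contradict each other. This also rests on the article alone; whether the conflict has any effect on the results depends on whether sound was playing, which the article does not say.

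The planned analysis is best called unadjusted rather than raw, since transformation is allowed.

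**What to change.** 1. Name BP, HR and S-AMY as the outcomes covered. Model the post-cannulation value with the same-session pre-value and the patient's mean pre-value as covariates, plus treatment and period. The patient mean is included so that the session-level slope is the within-patient one. If the outcome is transformed, put the pre-value on the same scale.
2. State three pre/post pairs per period for BP and HR, and one for S-AMY.
3. Reconcile Study protocol and Secondary outcomes to one defined BP/HR baseline reading, taken before any sound starts. Trial status reports 102 participants already randomised, so also state the timing actually used for them and note any differences between facilities. If sound was already playing at some readings, say so when reporting BP and HR.

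The cost is a change of analysis wording, best made before outcome data are examined by condition, and one clarified measurement step. No extra data are needed. The timing of past readings cannot be changed, only documented.
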